# A Web-Based Mindfulness-Based Cognitive Therapy for Couples Dealing With Chronic Cancer-Related Fatigue: Protocol for a Single-Arm Pilot Trial

**DOI:** 10.2196/48329

**Published:** 2023-11-06

**Keywords:** acceptability, cancer, chronic cancer-related fatigue, couple intervention, eMBCT, fatigue, feasibility, partners, pilot trial, web-based mindfulness-based cognitive therapy

## Abstract

**Background:**

Chronic fatigue is a common symptom among patients who have been treated for cancer. Current psychosocial interventions typically target the patient alone, despite growing evidence suggesting that a couples’ approach can increase and broaden the efficacy of an intervention. Therefore, based on an existing web-based mindfulness-based cognitive therapy for patients, the couple intervention COMPANION was developed.

**Objective:**

The primary objectives of this study are to determine the acceptability of COMPANION and its potential efficacy in reducing fatigue in patients with cancer. Our secondary objectives are to examine the feasibility of the trial procedures and the potential working mechanisms of the couple intervention.

**Methods:**

We will conduct a single-arm pilot trial for couples (ie, patients with cancer with chronic fatigue and their partners). All couples are allocated to the web-based couple intervention that consists of psychoeducation, mindfulness, and cognitive-behavioral exercises. The 9 sessions of the intervention are supervised remotely by a trained therapist. Patients and partners will complete questionnaires before starting the intervention (T0), 2 weeks after completing the intervention (T1), and 1 month after T1 (T2). They will also fill out weekly diaries during the intervention period. A subsample of patients (n≈5) and partners (n≈5) as well as all the therapists providing COMPANION will participate in the final focus groups. Benchmark values have been defined to determine the acceptability (ie, ≥60% of couples complete the intervention and/or ≥70% of the participants are satisfied with the intervention) and potential efficacy (ie, a significant improvement in fatigue and/or a clinically relevant improvement in fatigue in 45% of the patients between T0 and T1) of the intervention. The trial procedures are deemed feasible if an average of at least three couples are included per recruiting month and/or adherence to the assessments is at least 65% for T1 and the diaries and 60% for T2. To establish potential working mechanisms, changes in affect, sleep, catastrophizing, partner communication and interactions, self-efficacy, mindfulness, and closeness will be examined. Quantitative outcomes will be interpreted along with the results from the focus groups.

**Results:**

Data collection is expected to be completed by March 2024.

**Conclusions:**

This pilot trial will test the first web-based mindfulness-based cognitive therapy for couples targeting chronic cancer-related fatigue. Findings will indicate whether proceeding with a randomized controlled trial is warranted.

**Trial Registration:**

ClinicalTrials.gov NCT05636696; https://clinicaltrials.gov/study/NCT05636696

**International Registered Report Identifier (IRRID):**

DERR1-10.2196/48329

## Introduction

### Background

Chronic cancer-related fatigue (CCRF) is a common symptom among patients treated with curative [1-4] as well as palliative intent [5-7]. It can persist for many years and has a profound negative impact on patients’ quality of life [2,8,9]. Its etiology is likely multifactorial and includes several biological pathways [10,11]. According to the cognitive-behavioral model of CCRF, cancer and its treatment initially trigger fatigue, while cognitive-behavioral variables (eg, negative cognitions about fatigue and disrupted activity patterns) explain its persistence after completion of treatment [12-14]. Based on this model, cognitive-behavioral and mindfulness-based therapies have been developed to address CCRF. While these and other interventions have been shown to effectively alleviate patients’ fatigue [15-19], they are directed at the patient with cancer alone, despite growing evidence for the importance of involving patients’ partners in the treatment of CCRF (ie, a couples’ approach to treatment).

CCRF is experienced in the context of patients’ close relationships in multiple ways. First, the way patients and their partners interact in daily life is related to patients’ fatigue outcomes. For example, a daily diary study among survivors of cancer and their partners showed that partners’ facilitative reactions (eg, encouragement to be active) were related to better fatigue outcomes, while solicitous reactions (eg, taking over the patient’s chores) as well as ruminative conversations—fueled by patients and their partners maladaptive cognitions—were related to worse outcomes during the day [20,21]. This suggests that interventions encouraging adaptive daily interactions between couple members have the potential to contribute to better fatigue outcomes for the patient. Second, the degree to which patients benefit from cognitive behavioral therapy for fatigue appears to be related to partner and relationship variables. That is, a recent study [22] among patients with chronic fatigue syndrome showed that relationship dissatisfaction among patients and high fatigue in their partners are associated with less improvement in fatigue severity after therapy. Third, ample research shows that the cancer experience also impacts intimate partners. In particular, partners have been shown to experience substantial distress [23,24], which is positively related to patient fatigue [25,26], suggesting that an effective fatigue intervention can also benefit partners. Fourth, the aforementioned diary study [20] suggests that the way a partner deals with fatigue in the couple’s daily life is not only related to fatigue outcomes but also patients’ relationship satisfaction, with solicitous and facilitative responses being related to higher relationship satisfaction. Jointly, the evidence suggests that targeting the couple instead of the patient alone has the potential to increase the intervention’s effect on patient fatigue and broaden its impact to alleviate partner distress and benefit the couple’s relationship.

Based on this and studies indicating beneficial effects of interventions for couples coping with cancer in general [27-30], the study team has developed a couple intervention for dealing with CCRF called COMPANION (Dutch: Samen Minder Moe). The intervention is based on a web-based mindfulness-based cognitive therapy (eMBCT) that has been shown to be effective in reducing patient fatigue [31].

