**Potential mechanism variables**			
	Affect	5 items, shortened from [53]	Momentary
	Sleep	2 items, as in [53]	Last night^f^
	Catastrophizing	4 items, as in [21,53]	Last week
	Partner communication	3 items, based on [21]	Last week
	Partner interactions	6 items, shortened from [20]	Last week
	Self-efficacy	3 items, based on the SES^g^	Last week
	Mindfulness	4 items, based on the FMI^h^	Last week
	Closeness	2 developed items	Last week

^a^Patient only.

^b^Items ask the participants to report their current state (eg, “How fatigued do you feel right now?”).

^c^Partners report on their perception of patients’ fatigue.

^d^SFQ: Short Fatigue Questionnaire [54].

^e^Items ask the participants to report their state from the previous week.

^f^Items ask the participants to report their state from the previous night.

^g^SES: Self-Efficacy Scale [44].

^h^FMI: Freiburg Mindfulness Inventory Short Form [46].

Weekly fatigue severity in patients will be assessed with the 4-item Short Fatigue Questionnaire (SFQ) [54], a shortened version of the CIS-fatigue. The time frame has been adapted from the original past 2 weeks to the previous week, and items are formulated in the past tense (eg, “I felt tired”).

Current fatigue severity will be assessed in the weekly diaries with 1 item, “How fatigued do you feel right now?” that is scored on an 11-point Likert scale ranging from (score 0) “not at all” to (score 10) “as fatigued as I could be” [20,21,53].

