Based on the cognitive-behavioral model of fatigue and previous research [20,21,53,61], the potential mechanism variables are affect, sleep, catastrophizing, partner communication, partner interactions, self-efficacy, mindfulness, and closeness. A variable is established as a potential working mechanism of the couple intervention if its change (ie, improvement) over the course of the diary period covaries with decreases in weekly fatigue. Multilevel growth curve analysis will be applied to model the time slopes of the potential mechanisms and weekly fatigue over the entire diary period. We will explore both linear and nonlinear time trends and consider modeling random intercepts and random slopes. An improvement in fatigue and maladaptive constructs such as catastrophizing is indicated by a decrease over time. An improvement in adaptive constructs such as self-efficacy and mindfulness is indicated by an increase over time. For mechanism variables pertaining to partner communication and partner interactions, an improvement might be indicated by a decrease or increase. For some couples, talking (temporarily) more about fatigue is adaptive, while for others, talking (temporarily) less is adaptive. Covariances between the time slopes of the presumed mechanisms and the time slope of daily fatigue will be estimated to identify whether the temporal changes co-occur. A variable is established as a potential working mechanism in case the standardized covariance between the slope change factor for the outcome and that of the presumed mediators is significant (using a *z* test where ±1.96 is significant at the .05 level). Models will be run for weekly fatigue as well as weekly-reported momentary fatigue.

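### The mechanism plan leaves the direction of improvement open for partner interactions, although the protocol's own evidence points opposite ways for facilitative and solicitous reactions

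*Protocol article*

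**What the plan says.** **Rationale.** The Background section of the protocol article argues for a couple approach from a daily diary study. In that study "partners’ facilitative reactions (eg, encouragement to be active) were related to better fatigue outcomes, while solicitous reactions (eg, taking over the patient’s chores"), together with ruminative conversations, "were related to worse outcomes during the day [20,21". The same section adds a finding on a different outcome, "with solicitous and facilitative responses being related to higher relationship satisfaction".

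**Measurement.** Table 3 gives partner interactions one row in the weekly diary: "6 items, shortened from [20", the reference being to the diary study just described. Partner communication has its own row, with 3 items from reference 21.

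**Analysis.** Under Secondary Aims, "the potential mechanism variables are affect, sleep, catastrophizing, partner communication, partner interactions, self-efficacy, mindfulness, and closeness". A variable qualifies if "its change (ie, improvement) over the course of the diary period covaries with decreases in weekly fatigue". Maladaptive constructs should fall and adaptive ones should rise. The partner variables are exempted: "For mechanism variables pertaining to partner communication and partner interactions, an improvement might be indicated by a decrease or increase". The reason follows at once: "For some couples, talking (temporarily) more about fatigue is adaptive, while for others, talking (temporarily) less is adaptive".

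**Criteria.** Table 4 asks that time slopes differ significantly from zero and that improvements go together with improved fatigue, shown by a significant standardized covariance. Secondary Aims tests that covariance against ±1.96 and requires no sign.

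**The concern.** The reason given for the open direction is about how much a couple talks about fatigue. That is partner communication. It says nothing about whether a partner encourages activity or takes over chores, and on those reactions the protocol's own evidence does give a direction for fatigue. No reason is offered for leaving that direction open.

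This is a rule the article states, not a detail it leaves to a fuller document. With no sign on the mean slope, none on the covariance and none on improvement itself, no pattern of change in partner reactions counts against the hypothesis on the numerical criteria. That includes a shift the protocol's rationale associates with worse fatigue. Partner involvement is what COMPANION adds to the patient-centered therapy, and the Discussion says knowledge of mechanisms could make the intervention more efficient. A label of potential working mechanism should therefore mean something specific for this variable.

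**Working it through.** **1. The plan's own figure, used here only for n.** A one-sided paired t test with effect 0.5 and α = .05 gives power 0.812 at n = 27, so the stated 27 reproduces. 27/(1 − 0.20) = 33.75, so 34 couples also reproduces.

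**2. Sign patterns.** For solicitous reactions, taking the Background's associations as the expectation:

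| Mean slope | Covariance with fatigue slope | Reading | Meets the numerical criteria as written | Meets them with directions fixed |
|---|---|---|---|---|
| falls | positive | as expected | yes | yes |
| rises | positive | adverse shift, tracks worse fatigue | yes | no |
| falls | negative | association contrary to rationale | yes | no |
| rises | negative | association contrary to rationale | yes | no |

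For facilitative reactions the table is the mirror image: expected rise, negative covariance. All four patterns can pass as written; one of four passes once directions are fixed.

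In the adverse row the covariance already has the expected sign. Signing the covariance test alone would not exclude that row; the direction of the mean slope has to be set as well.

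**3. How often the adverse row would pass (illustration).** The documents give no slope means or correlations, so these are assumptions: a mean adverse slope of 0.5 SD of the person-level slopes (borrowing the protocol's medium effect), a correlation r of 0.3 to 0.6 with the fatigue slope, normal slopes, and true slopes treated as observed, which makes the probabilities too high.

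- *Slope criterion*, two-sided t test at .05 with effect 0.5: probability 0.706 at n = 27 and 0.808 at n = 34.
- *Covariance criterion*, Fisher z with m = atanh(r)·√(n − 3): P = 1 − Φ(1.96 − m) + Φ(−1.96 − m). Example with r = 0.5, n = 27: m = 0.549 × 4.899 = 2.691, so P = 1 − Φ(−0.731) = 0.768.
- *Both*, approximately the product of the two. A simulation with 100,000 replicates agreed to within about 0.01.

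| r | Covariance, n = 27 | Both, n = 27 | Covariance, n = 34 | Both, n = 34 |
|---|---|---|---|---|
| 0.3 | 0.329 | 0.23 | 0.407 | 0.33 |
| 0.4 | 0.546 | 0.39 | 0.655 | 0.53 |
| 0.5 | 0.768 | 0.54 | 0.864 | 0.70 |
| 0.6 | 0.924 | 0.65 | 0.971 | 0.78 |

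Example: 0.706 × 0.768 = 0.54. If the slope must lie in the expected direction, the slope criterion alone is met with probability below 0.00001 in this scenario. With no true mean slope, leaving direction open raises the chance of a significant slope counting as improvement from 2.5% to 5%.

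**The case against.** **The sentence may be meant benignly.** If the category holds both reaction types, a decrease or an increase could mean a decrease for one and an increase for the other. That reading is possible, and the plural (mechanism variables) fits it. It is weakened by the next sentence, which explains the open direction by differences between couples in talking, not by differences between types of reaction.

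**The words already guard against harm.** Secondary Aims wants improvement to covary with decreasing fatigue, and Table 4 wants it to accompany improved fatigue. A strict reader would refuse the adverse row on that wording. This stands as partial protection, but the stated tests do not enforce it, and improvement has no sign for this construct.

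**The evidence does not settle the direction.** The associations are within-day, the diary runs 17 to 22 weeks, and both reaction types went with higher relationship satisfaction. The first two facts limit how firmly directions can be set. The third concerns an outcome other than fatigue. Neither is the reason the plan gives.

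**Item content is inferred.** The article says where the six items come from, not what they ask. That they cover both reaction types is plausible from the source but not stated.

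**A stronger reading that does not hold.** A reader might infer from the single table row that facilitative and solicitous items are summed, so that opposite effects cancel and a real mechanism is missed. The article does not say the items are summed or how many are of each type, and scoring is commonly left to a full protocol or analysis plan. Cancellation would follow only if opposing items were added without reversing one set. Nor does the Background call solicitous reactions maladaptive; it uses that word for the cognitions behind ruminative conversations.

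**Conclusion.** The point holds and is minor. The two-way rule is justified for amount of talking but not for partner reactions, where the protocol's own evidence gives opposite directions for fatigue. As the criteria are written, a rise in solicitous reactions or a fall in facilitative ones that tracks worse fatigue can satisfy the slope and covariance tests.

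The probabilities rest wholly on assumed slopes and correlations and describe the numerical criteria only, without the verbal safeguard. They show that the gap is not negligible; they do not estimate how often it would occur in this trial. It would go too far to say that the plan would declare a harmful shift a success.

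The consequence is limited. This is one of eight listed mechanism variables under a secondary aim of a single-arm pilot, no critical value is attached to it, and the Benchmark and Critical Values section says the benchmarks are not definitive thresholds for proceeding.

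**What to change.** In Secondary Aims and the mechanism row of Table 4:

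- To the extent that the six items cover both types, name facilitative and solicitous reactions as separate mechanism variables.
- For the fatigue mechanism, define improvement as an increase in facilitative reactions with a negative covariance with the fatigue slope, and a decrease in solicitous reactions with a positive covariance.
- Keep the two-way rule for amount of talking about fatigue only.
- Report a significant change in the opposite direction as such, not as improvement.
- State that the expected directions come from within-day associations.

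The cost is a few sentences and possibly one extra score from items already collected. The downsides are possibly one more mechanism variable to test, and directions that rest on evidence at a shorter time scale than the weekly diary.

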### Research Aims

Given the relative novelty of this interventional approach, conducting a pilot trial is warranted. The primary aims of this pilot trial are (1) to determine the acceptability of the couple intervention and (2) to investigate its potential efficacy in reducing patient fatigue. Secondary aims are (3) to examine the feasibility of the trial procedures and (4) to determine the potential working mechanisms of the couple intervention.

## Methods

### Design

This study is a single-arm pilot trial among patients with cancer with CCRF and their partners. All included couples will be allocated to receive the COMPANION intervention, with a planned duration of 15-20 weeks. Couples will complete questionnaires and weekly diaries. Trial participation is estimated to take 6-8 months in total. Figure 1 presents a flowchart of the study.

**Figure 1 figure1:**
[figure not shown]
The study flowchart.

### Participants

Eligible participants are couples in which one member was diagnosed with cancer, completed cancer treatment for at least 3 months (excepting hormone therapy), and has been experiencing severe fatigue for at least 3 months. See Textbox 1 for an overview of all inclusion and exclusion criteria.

Inclusion and exclusion criteria for the study.
**Inclusion criteria**
The patient has received a cancer diagnosis (all malignancies are included).The patient completed cancer treatment with either curative or palliative intent ≥3 months earlier. Patients who currently receive hormone therapy are eligible.The patient experiences severe levels of fatigue (a score of ≥35 on the Checklist Individual Strength, subscale fatigue severity) at the screening.The patient has been experiencing severe fatigue for ≥3 months (as self-reported by the patient).The patient was 18 years of age or older at disease onset.The partner is 18 years of age or older.Both couple members live together.Both couple members have good command of the Dutch language (checked implicitly during registration).Both couple members have adequate computer literacy and have access to an internet-connected computer, laptop, or tablet (based on self-report).Both couple members agree to participate in the research.
**Exclusion criteria**
The patient is currently following an evidence-based therapy for chronic cancer-related fatigue (ie, cognitive behavioral therapy, mindfulness-based therapy, exercising, or physiotherapy) as self-reported at the telephone screening.The patient has a condition that can explain his or her fatigue and is potentially treatable (eg, anemia).The therapist decides, based on information collected during the intake session, that the intervention is not suitable for the couple. Criteria that will be considered include, but are not limited to:The presence of severe psychiatric morbidity such as suicidal ideation or psychosis (as assessed by the therapist at the intake session). Mild depression is not an exclusion criterion. A score of ≥20 on the hospital anxiety and depression scale at T0 is considered indicative of depression [32]. Therefore, if the patient or the partner scores ≥20, the therapist will determine at intake whether the participant has suicidal ideation or has another severe psychiatric morbidity. A participant (and thus the couple) will be excluded if, according to the therapist, that is the case.The presence of substance abuse, except for smoking.

### Recruitment

Recruitment will take place at the University Medical Center Groningen (UMCG), the Helen Dowling Institute (HDI), and through self-referral. At the UMCG, patients will be invited to the study by their oncologist or nurse, either at a follow-up appointment or during a phone call. Couples who indicate interest will be contacted by the research assistant. At the HDI, the research assistant will contact patients who are on the waiting list to receive patient-centered eMBCT and have given permission to be contacted for research purposes. Recruitment through self-referral will be encouraged by social media posts, newspaper articles, the panel of Kanker.nl [33], and flyers to be distributed at psychosocial care centers for people affected by cancer (Dutch: IPSO centra). Interested couples will be directed to the project website [34], where they can register.

### Screening

The research assistant will schedule a web-based call with all interested couples to further inform them about the study and screen their eligibility. During the screening process, reasons for ineligibility and decline of participation will be recorded in the recruitment log as they inform our secondary aim (ie, feasibility of trial procedures). Upon obtaining informed consent from the patient with cancer and their partner, the patient will receive a link through email to a survey to confirm fatigue- and cancer-related eligibility criteria.

